#### Source reconstruction

Individual anatomical MRI data will be processed using FreeSurfer for cortical surface reconstruction and brain tissue segmentation. Co-registration between MEG data and individual MRI will be performed using the facial point cloud. A forward model will be constructed using a boundary element model (BEM) based on each participant’s anatomical MRI. Source reconstruction will be performed using the dynamic Statistical Parametric Mapping method to obtain distributed source activity across the cortical surface.

#### Task-state analysis

For task-state data, brain activity will be extracted from event-related epochs spanning −500 ms to 1,500 ms relative to stimulus onset, with baseline correction applied from −200 ms to 0 ms. Source localization methods will be used to reconstruct brain activation at different time windows, thereby obtaining dynamic source-space responses during task execution. The analysis will focus on changes in activated brain regions during stimulus processing, phonological and language processing, and other task-related cognitive stages across different time points, thereby revealing the influence of acupuncture intervention on neural activity.

#### Resting-state analysis

For resting-state data, PSD values will be calculated for the delta (1–4 Hz), theta (4–8 Hz), alpha (8–13 Hz), beta (13–30 Hz), and gamma (30–80 Hz) bands. These values will be used to assess changes in spontaneous neural oscillatory activity after acupuncture. Source-level PSD will be analyzed to show the spatial distribution of spontaneous neural oscillatory activity. Functional connectivity in source space will be estimated with the phase locking index (PLI) to characterize large-scale brain network organization.

### Statistical analysis

For the resting-state PSD values, source-space neural activity, and whole-brain functional connectivity indices, both within-group and between-group comparisons will be performed. For within-group comparisons of pre- and post-acupuncture paired data, paired *t*-tests will be used. For between-group comparisons of the VA and SA groups, independent-sample *t*-tests will be employed. In whole-brain source-space statistical analyses, permutation-based cluster correction (≥5,000 permutations) will be applied to control for multiple comparisons and to identify brain regions with statistically significant differences.

For task-state data, time-window-based statistical methods will be used to compare brain activation intensity at different post-stimulus stages (time windows from 0 to 1,000 ms, in 100-ms steps). Linear mixed models will be applied to analyze condition effects and their interactions.

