### Sample size calculation

Currently, there is no unified standard for sample size calculation in MEG acupuncture research (37, 40). We will therefore enroll 40 healthy volunteers (20 per group). This sample size was informed by prior neuroimaging studies (41), in which 12–24 participants per group were used to examine brain activation differences between verum and sham acupuncture. Accounting for an anticipated 20% dropout rate, complete data are expected from at least 32 participants (16 per group).

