### Randomization

Participants will be randomly assigned to the verum acupuncture (VA) group or the sham acupuncture (SA) group in a 1:1 ratio. The random allocation sequence will be generated using block randomization, stratified by sex, to ensure a balanced distribution of male and female participants across both groups. Allocation concealment will be maintained by having the research coordinator obtain the participant’s intervention assignment from sequentially numbered, opaque, sealed envelopes immediately before the first intervention session, and communicate this information exclusively to the acupuncturist.

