### Outcome measures

#### Primary outcome

The primary outcome is the change in MEG signals before and after acupuncture intervention. MEG data will be collected during the resting state, acupuncture state, and language task state to evaluate the central effects of acupuncture. Specific MEG metrics include power spectral density (PSD) across different frequency bands (delta: 1–4 Hz, theta: 4–8 Hz, alpha: 8–13 Hz, beta: 13–30 Hz, gamma: 30–80 Hz), source-space neural activity, and whole-brain functional connectivity.

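### Resting-state, source-space and connectivity comparisons: the between-group t-test has an unnamed variable and no baseline or sex adjustment, and it is not ranked above the within-arm tests

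*Protocol article*

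**What the plan says.** The Statistical analysis section of the protocol article states that for the resting-state PSD values, source-space activity and whole-brain connectivity indices "both within-group and between-group comparisons will be performed". Within each arm, pre and post data are compared by paired t-tests. Between arms: "For between-group comparisons of the VA and SA groups, independent-sample *t*-tests will be employed". Whole-brain source-space analyses use permutation-based cluster correction with at least 5,000 permutations. Task-state data are handled separately, by time windows and linear mixed models with interactions.

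Three other sections bear on this:

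- Primary outcome: "The primary outcome is the change in MEG signals before and after acupuncture intervention". The metrics listed there are the ones to which the t-tests apply.
- Randomization: "The random allocation sequence will be generated using block randomization, stratified by sex".
- Sample size calculation: 40 participants, 20 per group, are enrolled. With 20% dropout, 32 (16 per group) are expected to have complete data. The number rests on precedent: "This sample size was informed by prior neuroimaging studies (41), in which 12–24 participants per group were used".

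The Statistical analysis section does not name the variable entering the between-group t-test, a covariate for it, or which of the two kinds of comparison decides whether verum differs from sham.

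**The concern.** In a randomised, sham-controlled trial, only the verum-sham (VA-SA) contrast separates the effect of acupuncture from whatever else happens during the session. The Assessment timepoints section describes a long sequence: language tasks, a resting scan, seven single-acupoint acquisitions with washouts, then the multi-acupoint condition. Drowsiness, drift and repeated scanning can move both arms. A paired test within one arm cannot tell such a shift from an acupuncture effect. Two paired tests read side by side can easily disagree by chance when the arms have changed equally.

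The contrast that does answer the question is tested without the participant's own pre-needling value as a covariate and without the stratification factor. With 16 to 20 per arm, precision is scarce, and the baseline recording and sex are already collected. The test is named in this text, so an analysis plan that follows it would inherit the choice.

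**Working it through.** **The plan's own figure.** 40 × (1 − 0.20) = 32, or 16 per group, which reproduces the stated number. No effect size, SD, alpha or power is given, so there is no power calculation to reproduce.

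**Assumptions not in the document.** Two-sided alpha 0.05, 80% power, equal variance before and after needling, pre-post correlation r of 0.5, 0.7 or 0.8. For detectable differences, one SD is the between-person SD of a single recording.

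**Precision of the VA-SA contrast.** Residual variance relative to a post-value t-test (= 1):

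- change score: 2(1 − r)
- post value adjusted for baseline: 1 − r²

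The reduction from adjustment is therefore r² against post values, and 1 − (1 − r²)/[2(1 − r)] = (1 − r)/2 against change scores.

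| r | Change | Adjusted | Cut vs post | Cut vs change |
|---|---|---|---|---|
| 0.5 | 1.00 | 0.75 | 25% | 25% |
| 0.7 | 0.60 | 0.51 | 49% | 15% |
| 0.8 | 0.40 | 0.36 | 64% | 10% |

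**Detectable difference, 16 per arm, r = 0.7** (noncentral t):

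- post-value t-test: 1.02 SD
- change-score t-test: 1.024 × √0.60 = 0.79 SD
- adjusted, ignoring the cost of the covariates: 1.024 × √0.51 = 0.73 SD
- adjusted, with 28 instead of 30 degrees of freedom and an allowance of 1 + 1/28 in the variance for chance baseline imbalance: 1.026 × √(0.51 × 1.036) = 0.75 SD

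**Power, 16 per arm, assumed true difference 0.8 SD.** The post-value t-test has 59% at every r. The adjusted column is a simulation of 6,000 runs with baseline and sex in the model.

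| r | Change-score t-test | Adjusted for baseline and sex |
|---|---|---|
| 0.5 | 59% | 70% |
| 0.7 | 81% | 85% |
| 0.8 | 93% | 94% |

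With no true difference, all three analyses rejected in about 5% of simulated trials.

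**Two within-arm tests side by side.** Let p be the chance that a paired t-test with n = 16 is significant when both arms have the same true shift, in SDs of the change. VA-only significance then has probability p(1 − p).

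| Common shift | p | VA significant, SA not |
|---|---|---|
| 0 | 0.050 | 0.050 × 0.950 = 4.8% |
| 0.25 SD | 0.155 | 0.155 × 0.845 = 13% |
| 0.5 SD | 0.465 | 0.465 × 0.535 = 25% |
| 0.75 SD | 0.801 | 0.801 × 0.199 = 16% |
| 1.0 SD | 0.962 | 0.962 × 0.038 = 4% |

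A split in either direction is twice as likely. These are rates for one uncorrected test. The maximum of p(1 − p) is 25%, so the 0.5 SD row is close to the worst case.

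**The case against.** A reader might infer that the plan discards the baseline recording. The text does not support that. The primary outcome is a before-after change, so the natural reading of the between-group test is a t-test on changes, which uses the baseline, as do the paired tests. What can be said is that the variable is not named and baseline is not a covariate. On the change-score reading the loss is modest when r is high: 81% against 85% power at r = 0.7, and 93% against 94% at r = 0.8. It is material at r = 0.5 (59% against 70%). The larger reductions apply only if post values are compared.

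A reader might also infer that the planned test is invalid, or that the plan will lead to a false verum-specific claim. Neither follows. The unadjusted t-test holds its type I error, a direct VA-SA test is planned, and the Abstract states the aim as a comparison of verum with sham. No sentence rests an effect on within-arm significance. The risk comes from the missing ranking of the two kinds of comparison. Cluster correction limits error within a map, but it does not make a comparison of two arms' significance maps a test of their difference.

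Within-arm results also serve a stated purpose, since the Background wants a normative description of responses in healthy volunteers. That argues for keeping them under a clear label. Finally, a condensed article may leave covariates to an analysis plan that is not shown. That lowers the severity, but the test itself is fixed here with no mention of adjustment.

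**Conclusion.** The point holds for resting-state PSD, source-space activity and connectivity. The task-state mixed models are outside it. The between-group test is valid but underspecified and less precise than the collected data allow. At r = 0.7 and 16 per arm, the 80%-power detectable difference would fall from about 0.79 SD (change) or 1.02 SD (post) to about 0.73–0.75 SD. Without a stated ranking, side-by-side within-arm tests carry a VA-only false impression in roughly 5%, 13%, 25%, 16% and 4% of cases at common shifts of 0, 0.25, 0.5, 0.75 and 1.0 SD.

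All of these figures rest on assumed alpha, power, correlation and shift, none of which the document gives. No separate gain is claimed for the sex term, whose inclusion aligns the analysis with the stratified randomisation. For any r strictly between 0 and 1, adjustment lowers residual variance under either reading, before the small cost in degrees of freedom. Severity: should-fix.

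**What to change.** In the Statistical analysis section:

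1. State that the VA-SA contrast is the sole basis for any verum-specific conclusion.
2. Estimate it, per vertex, region or connection, by regressing the post-needling value on group, the recording taken before that needling condition, and sex. Name that recording for each condition, because the schedule contains several resting scans.
3. Test the group coefficient with the planned 5,000 or more permutations and cluster correction, permuting the residuals of the model without group (Freedman-Lane) within sex strata.
4. Label within-arm changes as descriptive or secondary, and state that they are not evidence of a verum-sham difference.

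The cost is two degrees of freedom and a change to the wording and the analysis script. No new data are needed. The change should be made before any unblinded analysis.

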### Safety monitoring and adverse events

Safety evaluation will include general physical examination and assessment of adverse reactions. Potential adverse events related to acupuncture may include subcutaneous hematoma, minor post-needling bleeding, and needle fainting. Should any adverse events occur due to the procedure, appropriate examination and symptomatic treatment will be provided, and the participant and their family members will be informed accordingly.

All adverse events will be documented in detail, regardless of their perceived relationship to the study, including the time of onset, signs and symptoms, laboratory findings, management and outcomes, follow-up duration, severity, and duration. Concomitant medication use will also be recorded to facilitate analysis of the relationship between adverse events and the study intervention. Serious adverse events will be reported in compliance with institutional regulations.

### Data management and quality control

All raw MEG data, preprocessed data, and associated behavioral information will be stored following a standardized data management protocol. Data files will be anonymized using participant identification numbers, and all personally identifiable information will be removed to ensure data security and privacy protection. All data will be stored on encrypted servers with multi-level access controls and regular backups to prevent data loss. Preprocessing pipelines, analysis scripts, and parameter settings will be recorded using version control systems to ensure reproducibility and traceability.

### Ethics and dissemination

This study has been approved by the Ethics Committee of the First Teaching Hospital of Tianjin University of Traditional Chinese Medicine. Written informed consent will be obtained from all participants prior to enrollment. Participants will be free to withdraw from the study at any time without penalty. Study results will be disseminated through peer-reviewed publications and presentations at academic conferences.

## Discussion

### Treatment advances and research bottlenecks in acupuncture for post-stroke aphasia

Despite accumulating evidence supporting acupuncture for post-stroke aphasia, major research bottlenecks remain. In our previous work, a sham-controlled trial (10) published in 2024 demonstrated clinically meaningful improvements with XNKQ acupuncture that were sustained through 6 months. However, the broader literature (43, 44) is still frequently constrained by small sample sizes and methodological limitations, such as inadequate blinding and heterogeneous outcome measures. In addition, optimal acupuncture parameters have yet to be defined, including point selection, stimulation intensity, treatment frequency, and treatment duration. Crucially, the central neural mechanisms through which acupuncture modulates language function remain incompletely understood, thereby limiting rational protocol optimization and the development of patient selection strategies (12).

### Rationale for studying healthy volunteers

This mechanistic study was conducted in healthy volunteers to reduce sources of variation that are difficult to control in stroke populations. After stroke, neural responses are shaped by lesion location, lesion size, and time since onset, and patterns of language network reorganization can differ substantially across individuals (23, 45). This makes it difficult to separate acupuncture-related effects from lesion-related changes and spontaneous recovery. In healthy participants, brain responses to acupuncture can be examined under more stable conditions and with fewer confounding influences, such as stroke-related brain injury, medication use, and disease-related neural reorganization. This may allow clearer identification of neural signatures associated with acupuncture and may also help define dose–response relationships between stimulation parameters and brain activity (46). In addition, studies in healthy volunteers allow tighter experimental control, repeated measurements, and more systematic adjustment of acupuncture parameters than is usually feasible in patient populations (47). Findings from healthy participants may therefore provide a useful reference for later studies in patients.

### Advantages and challenges of OPM-MEG in acupuncture research

To our knowledge, this is the first study to apply OPM-MEG to the investigation of acupuncture mechanisms. OPM-MEG provides millisecond temporal resolution, which makes it possible to track the time course of brain responses during acupuncture. Neural effects can therefore be examined across different timescales, from immediate responses during needle manipulation to more sustained changes after needle removal (25, 26). Unlike hemodynamic imaging methods such as fMRI (48), MEG records neuronal currents directly rather than secondary vascular responses. This offers a more direct view of how acupuncture influences neural activity. It is particularly relevant in acupuncture research, where the timing of neural events may be important for understanding mechanism and where hemodynamic responses may not fully reflect the underlying neural process. OPM-MEG also has practical advantages over conventional SQUID-based systems. The closer sensor-scalp distance may improve sensitivity and spatial resolution. The system can also be adapted more easily to different head sizes and is more tolerant of participant movement during scanning (28, 29). These features are useful for acupuncture studies, where participant comfort and relatively natural experimental conditions are important for eliciting authentic neural responses and *deqi* sensations.

Several challenges should also be considered. MEG is mainly sensitive to tangential cortical sources and is less effective for detecting activity in deep brain structures such as the thalamus and basal ganglia, which are relevant to language processing and may also be influenced by acupuncture (21). In previous MEG studies of acupuncture, variation in study design, analytical methods, and sample size has contributed to inconsistent findings (47). Standardized MEG acquisition and analysis protocols for acupuncture research are not yet established. In addition, the relationship between MEG findings and clinical outcomes still requires further validation (49). Multimodal approaches combining MEG and fMRI may therefore provide a more complete account by drawing on the strengths of both methods (50).

### Language task paradigms in acupuncture mechanism research

The use of language tasks together with MEG provides a useful approach for studying how acupuncture affects language-related neural networks. Tasks such as picture naming and word repetition engage core components of language processing, including lexical-semantic access, phonological encoding, and speech motor programming. They also produce reliable activation in known language regions, including Broca’s area, Wernicke’s area, and the pathways connecting them (51). Compared with resting-state approaches, task-based neuroimaging has several advantages. It probes neural systems directly relevant to aphasia, helps clarify how acupuncture influences neural processing during active language production and comprehension, and allows comparison of acupuncture-related effects across different language domains (22, 52). Recent work suggests that language recovery is multidimensional. Fluency, semantic-executive function, and phonology may follow different recovery trajectories and rely on partly distinct neural substrates. Acupuncture-related effects may therefore differ across language components. This possibility can be examined by combining multiple language tasks with MEG recording (53, 54).

### Single-point versus multi-point effects in XNKQ acupuncture

An important question in this study is whether acupoint combinations produce effects beyond those of individual points. Neuroimaging work by Zhang et al. showed that stimulation at LR3 combined with KI3 activated a broader set of brain regions than stimulation at LR3 alone. Additional activations were found in the posterior cerebellar lobe and Brodmann area 6 (BA6), and BA6 was uniquely engaged under the combined LR3 plus KI3 condition (33). In animal studies, Jiang et al. reported that electroacupuncture at ST36 and GB30 produced stronger analgesic effects through activation of the endocannabinoid system, whereas this effect was not observed with single-point stimulation (34). Building on these findings, the present study compares neural activation during single-point stimulation with that observed during the complete XNKQ formula. This comparison may help identify formula-specific activation patterns, clarify the relative contribution of individual points to language network modulation, and explore possible synergistic effects within acupoint combinations. It may also inform future refinement and personalization of the XNKQ protocol.

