Recent advances in optically pumped magnetometer-based MEG (OPM-MEG) have opened up new possibilities for this field. Compared with conventional SQUID-based MEG systems, OPM-MEG operates at room temperature, can be adapted more easily to different head sizes, and is more tolerant of participant movement during scanning. It may provide improved sensitivity and spatial resolution (27, 28). The availability of domestically developed OPM-MEG systems has improved the feasibility of this line of work (29). Current evidence suggests that OPM-MEG performs comparably to, and in some settings better than, SQUID-MEG across a range of neuroimaging paradigms. In particular, triaxial OPM configurations can capture approximately twice the total signal and provide better interference rejection than conventional single-axis systems (30–32).

Against this background, the present study will use OPM-MEG to investigate both resting-state and language task-related brain activity in healthy volunteers receiving XNKQ acupuncture. This work may help address an important gap in current mechanistic research. By comparing single-point and multi-point stimulation, the study will examine the neural basis of acupoint combination, as previous findings suggest that multi-point prescriptions may induce broader neural activation and engage additional neurochemical pathways than single-point stimulation (33, 34). The relationship between *deqi* sensation and MEG signals will also be examined. Earlier fMRI studies support this line of inquiry by showing that *deqi* is associated with activation in the limbic-paralimbic-neocortical network, including the thalamus, parahippocampal gyrus, insula, and cingulate cortex (35, 36). As a first step, this study characterizes the normal spatiotemporal patterns of cerebral magnetic responses to Xingnao Kaiqiao acupuncture and language tasks in healthy volunteers. Because these responses reflect the language-related networks targeted by acupuncture, they provide a normative reference for subsequent investigations in patients with post-stroke aphasia.

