#### Assessment timepoints

The assessment will proceed in the following sequence. First, during the baseline period, participants will complete language tasks with simultaneous MEG recording. Second, a resting-state MEG scan will be performed after the language tasks and before the first acupuncture intervention. Third, the acupuncture state assessments will follow a sequence of single-acupoint needling first and then multi-acupoint needling.

In the single-acupoint sequence, after completing the language task and resting-state MEG scans, each acupoint will be needled individually, completing a total of seven acupuncture-state data acquisitions (CV23 and its auxiliary acupoints Beside CV23 are needled simultaneously and recorded as a single acquisition). For acupoints requiring 30-min needle retention (GV26, SP6, CV23, and Beside CV23), MEG data will be collected during the retention period, followed by a resting-state acquisition after needle removal. For acupoints without needle retention (PC6, HT1, LU5, and BL40), an immediate post-needling MEG acquisition will be performed. The interval between successive acupoints will follow the washout period determined in the pilot study.

In the multi-acupoint sequence, after all single-acupoint sessions are completed and the washout period has elapsed, a resting-state MEG scan will be performed. Subsequently, all acupoints will be needled simultaneously as a group, with MEG data collected during the retention period. After needle removal, a final resting-state MEG scan will be conducted to assess the overall central mechanism of the full Xingnao Kaiqiao acupuncture.

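### A difference between the full formula and a single point cannot by itself show synergy or a formula-specific effect, because point effects that merely add also produce it

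*Protocol article*

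**What the plan says.** The Background announces the aim: "By comparing single-point and multi-point stimulation, the study will examine the neural basis of acupoint combination". The Discussion section on single-point versus multi-point effects repeats it as a question, "An important question in this study is whether acupoint combinations produce effects beyond those of individual points", and names the comparison: "the present study compares neural activation during single-point stimulation with that observed during the complete XNKQ formula". From that comparison the authors hope to identify activation specific to the formula and to "explore possible synergistic effects within acupoint combinations". The section on implications for future research adds that such differences may guide refinement of the protocol.

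Under Assessment timepoints, each participant has the points needled one at a time, "completing a total of seven acupuncture-state data acquisitions". The formula comes last: "all acupoints will be needled simultaneously as a group, with MEG data collected during the retention period".

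The Statistical analysis section names paired t-tests ("For within-group comparisons of pre- and post-acupuncture paired data") and independent-sample t-tests ("For between-group comparisons of the VA and SA groups"). Mixed models appear in the task-state paragraph without a definition of the conditions, and the only timing given for the language tasks is the baseline period. No test, null hypothesis or additive reference is named for formula versus single point.

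**The concern.** An effect beyond the individual points has to be judged against what those points would produce together without interaction. On a magnitude scale that reference is the sum of their separate effects. Setting the formula against one point uses a different reference, namely that the other points contribute nothing. If two or more points act in the same direction, the formula exceeds any one of them even when nothing interacts.

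The amount of stimulation also differs. By Table 1 a single acquisition uses one needle (GV26), two (a bilateral point) or three (the CV23 set), and the formula uses 2+1+2+2+2+2+1+2 = 14. The problem would remain with perfect washout and random order.

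At stake is an aim the authors call important. Ordinary summation could be reported as synergy and carried into refinement of the protocol. So could saturation, where the formula does less than the sum of its points but more than any one of them.

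**Working it through.** **The plan's own figure.** The Sample size section gives 40 participants and 20% dropout: 40 × 0.80 = 32, or 16 per group. This reproduces. The article states no power, effect size, alpha or standard deviation, so the rest is assumed.

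**Assumptions.** There is one measure, without correction for multiplicity, at two-sided 5%. Change scores have SD 1, and ρ is the correlation between one person's change scores (0 or 0.5). Each of the seven acquisitions shifts the measure by the same d, and the formula shifts it by exactly 7d, so true synergy is zero.

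**Formula minus one point, within verum, n = 16.** The mean difference is 7d − d = 6d and its SD is √(2(1−ρ)), that is 1.41 at ρ = 0 and 1.00 at ρ = 0.5. The noncentral t distribution gives the chance of a significant result favouring the formula:

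| d | ρ = 0 | ρ = 0.5 |
|---|---|---|
| 0.05 | 12% | 20% |
| 0.1 | 35% | 61% |
| 0.2 | 89% | 99% |

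The chance passes 50% at d = 0.12 (ρ = 0) or 0.09 (ρ = 0.5). At those effects a single point's own pre/post test has only about 5% to 7% power.

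**Same difference, verum versus sham, 16 per group.** Assume the sham changes are zero on average. The mean is still 6d, and the t-test has 30 degrees of freedom. At ρ = 0.5 the formula is favoured in 38% (d = 0.1) and 91% (d = 0.2); at ρ = 0, in 21% and 64%. Subtracting sham removes non-specific effects, but it does not stop the verum effects from summing.

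**Fewer active points.** If only two act, the formula shifts the measure by 2d and the difference from one of them is d. At ρ = 0.5 and n = 16 the formula is favoured in 11% (d = 0.2), 47% (d = 0.5) and 85% (d = 0.8). If only one acts, formula versus that point stays at 2.5%.

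**Saturation.** Let the formula effect be 4d with d = 0.3, so the difference is 3d = 0.9. At ρ = 0 and n = 16 the formula still beats one point in about two thirds of trials, although it falls short of the sum.

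**Additive contrast.** Take formula minus the sum of the seven single changes. Its variance is 8 + 2ρ(21 − 7) = 8 + 28ρ, where 21 is the number of pairs among the single changes and 7 the number of pairs with the formula. The SD is √8 = 2.83 at ρ = 0 and √22 = 4.69 at ρ = 0.5. In simulation at ρ = 0.5 with zero synergy it favours synergy in 2.3% to 2.7% of runs, against a nominal 2.5%. Within verum at n = 16, 80% power needs a noncentrality of about 3.00, so the detectable synergy is 3.00 × 2.83/√16 = 2.1 SD (ρ = 0) or 3.00 × 4.69/√16 = 3.5 SD (ρ = 0.5). Between arms it is about 2.90: 2.90 × 2.83/√8 = 2.9 SD or 2.90 × 4.69/√8 = 4.8 SD.

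**The case against.** A reader might infer that the plan tests whether the formula equals one point, and that it will usually report false synergy. The article supports neither statement. Its Statistical analysis section names no formula-versus-single test, and a statistical analysis plan that is not shown could define one. The synergy wording is tentative and attaches to neither the primary nor the secondary outcome. How often the comparison misleads rests on assumed effects: seven equal effects in one direction are not documented, the Background cites point-specific effects, and Table 1 mixes reducing and reinforcing techniques. Effects of opposite sign, and the planned cluster correction in whole-brain analyses, would lower the rates. All of this stands.

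The needle count also needs care. The formula is recorded during retention, and Table 1 gives four of the points no retention. If that applies to the formula, 1 + 2 + 3 = 6 needles are in place at that time, not 14. Six is still more than any single acquisition has.

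A further objection is that the authors may mean spatial novelty: a region engaged only by the combination, as in the human imaging study they cite. Where no single point acts, the additive prediction is zero and a formula response there would be informative. That is fair in principle. But a region where each point has d = 0.1 would look silent in each single-point test (about 6% power). Under additivity the formula shift there is 0.7 SD, close to the 3.00/√16 = 0.75 SD detectable with 80% power. The absence of a significant single-point result therefore does not establish the additive prediction of zero.

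Finally, the additive contrast is no cure-all. It is noisy, its null changes between raw and log power, and a sum of seven changes has no natural meaning for a bounded connectivity index. These objections limit the remedy. They do not make the simple comparison informative about synergy.

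**Conclusion.** The concern holds in a limited form. The comparison described in the Discussion cannot by itself show an effect beyond the individual points, because summation of same-direction effects produces the same result, and the sham arm does not separate the two. This conclusion is logical and needs no assumed effect size.

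The rates are conditional on the assumptions listed above. They can be high when all seven acquisitions act alike and low when only one or two points act weakly. The article gives no basis for choosing between these cases, so the defensible statement is that the comparison can readily suggest synergy where there is none.

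**What to change.** In the Discussion section on single-point versus multi-point effects, and in the Statistical analysis section, state that formula-versus-single differences are descriptive. They show the response to more stimulation than one point gives, and they are not evidence of synergy or of a formula-specific effect.

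Make a synergy claim only from an exploratory contrast computed per participant: the formula change minus the sum of the seven single-acquisition changes. Name the scale (for example log power, not a bounded connectivity index), and compare the contrast between verum and sham with its confidence interval. If that is judged too imprecise, remove the claim.

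The cost is wording and a modest analysis. The downside is a wide interval, given the detectable sizes shown above. The contrast also remains limited by three features of the schedule. The formula always comes last. The recording windows differ: immediate post-needling for four acquisitions, retention and post-removal for the rest and for the formula. And no resting scan is stated before each single point, only before the first point and before the formula. These limits should be reported with the result.
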